### Study protocol

A common protocol and manual of operations have been developed covering all aspects of the study for utilization by all sites. Obstetric and newborn care are delivered according to local practices and standards at the individual clinical sites. Trained study personnel perform all study-related procedures. Training procedures and evaluation methods have been developed and are utilized under the supervision of the Study Principal Investigators, to ensure consistency between sites. Within each site, implementation of general study procedure training is the responsibility of the Site Principal Investigator and Study Coordinator for each site. Quality control checks (via re-abstraction) are performed for primary outcomes by site Principal Investigators on randomly selected charts with and without adverse outcomes.

Study visits typically coincide with regular obstetrical care visits. Attempts are made to collect one prenatal urine sample and one prenatal buccal sample at each pregnancy trimester to assess urinary concentration levels and epigenetic alterations that may be occurring throughout pregnancy. Pregnancy trimesters are defined as first trimester (through 13 weeks), second trimester (14–27 weeks), and third trimester (28–42 weeks). Biospecimen collection and questionnaire data collection are administered separately from obstetric and neonatal clinical care. Biospecimen collection timing was chosen to facilitate evaluation of longitudinal/trimester effect of associations between herbicide concentrations and outcomes. Study adherence is incentivized by compensation to participants for their time and effort. The amount and types of compensation are determined in advance and are consistent across all sites throughout the study.

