### Study visits and specimen collection

The first prenatal specimen collection ideally occurs prior to 13 weeks’ gestation. If a participant is recruited after 13 weeks’ gestation, then first prenatal collection occurs as soon after enrollment as possible. At this study visit, site coordinators collect prenatal urine and buccal samples from the primary participant. If the primary participant consents to recruitment of the other biological parent, then the study coordinator also will approach the other biological parent for written informed consent. If given, they will collect buccal and urine specimens from the secondary participant, if consented. The study coordinator will email links to participants to complete pre-conception, food frequency, and stress questionnaires electronically. Study personnel conduct prenatal/medical chart reviews and contact participants for follow-up if needed.

The second prenatal collection occurs at the first prenatal visit that is between 14- and 27-weeks’ gestation and at least 4 weeks after the first prenatal collection while the third prenatal collection occurs at the first prenatal visit that is after 28 weeks’ gestation and at least 4 weeks after the second prenatal collection, if practicable. Collection of a specimen outside the ideal time frame is preferred over not collecting a specimen. Study team members collect a urine sample from the primary participant and email the primary participant links to food frequency and stress questionnaires. If applicable and not yet collected, they attempt to collect buccal and urine samples from the other consented biological parent and complete the pre-conception questionnaires with both participants if not previously administered. They conduct prenatal/medical chart reviews and contact participant for follow-up if needed.

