### Exposure assessment

Coded urine and buccal samples collected at clinical locations will be transported to study site laboratories for processing per laboratory processing protocols and aliquoted into cryovials (as appropriate) and stored. Buccal and urine samples will be stored locally at ≤ -20 °C until they are shipped to the Indiana Bioservices biorepository in Indianapolis, Indiana, where they will be stored ≤ -70 °C. Samples will be batch shipped from Indiana Bioservices to an external analytic laboratory for completion of relevant assays. Details of the analytic methods utilized for biochemical concentration will be detailed in other manuscripts.

This study will utilize Geographical Information Systems and remote sensing data to develop herbicide exposure index estimates to complement biomonitoring results. An herbicide exposure index will be calculated using a buffer zone around a consenting participant’s residence. Using methods described in GIS-based exposure studies [46, 47], ArcGIS (ESRI Inc. Version 10.6.1) will be used to calculate the total land area within each the buffer zone for each crop type, which will be compiled based on USDA crop land use data [48]. The total area of each crop will be then multiplied by an average pesticide application rate estimated from data available from the USDA Chemical Use Program [49]. The total area of crop use land in each participant buffer zone (in km^2^) will be multiplied by the amount of pesticide application rate (in kg/km^2^) for each crop in order to estimate the total volume (in kg) of each pesticide applied within the buffer zone. An exposure index will be calculated for each pesticide expected to have been used. In addition, an aggregate exposure index will also be estimated. Herbicide exposure metrics will be utilized as an adjunct to biomarker analysis to evaluate relationships between geographic exposure and biomarker levels, as well as to refine associations between aggregate exposure and health outcomes.

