Descriptive statistics, including appropriate parametric and semiparametric methods, will be used for continuous, binary, ordinal, and polytomous variables to describe characteristics of the cohort, exposures, and outcomes. We will examine the concentration data for appropriateness of cutoff values (quartiles, quintiles, high/low, etc.) or use as a continuous variable. Examples of statistical modeling approaches that we intend to utilize include least-squares linear regression, which will be used to describe the unadjusted associations between continuous outcomes (e.g., length of gestation or birthweight) and longitudinal exposure variable; and logistic regression, which will be used to describe the unadjusted association between a dichotomous outcome (e.g., diagnosis of pre-eclampsia or gestational diabetes, presence of congenital anomaly) and longitudinal exposure variables. Multivariate models will also be fit using suitable stratification and modeling adjustments for confounding and assessments of effect modification to evaluate associations between each outcome and multiple longitudinal exposures using methods appropriate to the structure of the data and analyses [62]. We will begin with simple multiple logistic regression models but will adjust to other appropriate models based on the data. To evaluate for the presence of exposure misclassification, an exposure matrix variable utilizing both biomarker and geospatially derived exposure estimates will be modeled with respect to each outcome [63].

Confounding variables have been determined a priori based on prior studies. Potential confounding factors to be considered are maternal age [64, 65], country of birth [66, 67], race/ethnicity [68, 69], height and preconception weight (including Body Mass Index) [70, 71], pregnancy weight gain [72, 73], marital status [64, 74], employment status [75, 76], socioeconomic status [77, 78], education level [78, 79], smoking status [80, 81], insurance coverage [82–84], alcohol use [85, 86], drug use, caffeine use [87], history of fetal loss and gestational age at loss [88], parity [89, 90], prenatal care [91], and rurality [92, 93]. As we will have residential address information, we will be able to explore the impact of location-based markers of social determinants of health such as distance to health care facilities, area deprivation, green space, and others.

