## Challenges and anticipated responses

While the Heartland Study is anticipated to be a relatively large cohort of at least 2000 pregnancy dyads, it may still be underpowered to identify associations between herbicides and some rare outcomes, such as stillbirth and specific congenital anomalies. Aggregation of related outcomes may be used to improve power where appropriate. For example, it may be appropriate to evaluate fetal death as an aggregate variable including stillbirth and miscarriage, which occur on a spectrum. Related congenital anomalies may be aggregated to achieve statistical power if appropriate.

This study is poised to make an important contribution to the existing knowledge about herbicide concentration. There may be limitations in the ability to detect important seasonal variations in concentration and sensitive windows for exposure, although recurrent urine samples are being collected throughout pregnancy and aggregate batches by phases of the growing season will be evaluated. The study will utilize the latest advancements in analytic techniques for urine biomarker analysis, providing an objective assessment of concentration. Multi-exposure modeling will be used to examine the combined effects of herbicide exposure. Geographic estimates of exposure will be used to augment biomarker data and allow for a more multidimensional exposure assessment. Through combined application of the techniques, the Heartland Study will fill important gaps in knowledge about herbicide exposures in the Midwest.

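### As worded, modelling a combined biomarker and GIS exposure matrix against each outcome cannot evaluate exposure misclassification; the repeat urines already collected can, within limits

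*Protocol article*

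**What the plan says.** The Statistical analysis section puts an aim and a method in one sentence. The aim comes first: "To evaluate for the presence of exposure misclassification, an exposure matrix variable". The method follows: "an exposure matrix variable utilizing both biomarker and geospatially derived exposure estimates will be modeled with respect to each outcome". A reference is cited for it.

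Other sections describe the two measures:

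- **GIS index (Exposure assessment).** It is the area of each crop in a buffer around the home, "multiplied by an average pesticide application rate estimated from data available from the USDA Chemical Use Program". Its role is secondary: "Herbicide exposure metrics will be utilized as an adjunct to biomarker analysis". The same sentence plans to relate geographic exposure to biomarker levels, which compares the two measures without any outcome.
- **Urines (Study protocol).** "Attempts are made to collect one prenatal urine sample and one prenatal buccal sample at each pregnancy trimester". The second is to be taken "at least 4 weeks after the first prenatal collection" (Study visits and specimen collection), and the third is spaced in the same way from the second, where practicable.
- **Stated uses of the repeat urines.** The timing was chosen "to facilitate evaluation of longitudinal/trimester effect of associations between herbicide concentrations and outcomes" (Study protocol). Under Challenges and anticipated responses, "recurrent urine samples are being collected throughout pregnancy and aggregate batches by phases of the growing season will be evaluated". Within-woman reliability is not among these uses.

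**The concern.** Misclassification is a property of the link between measured and true exposure. An outcome regression observes only the link between measured exposure and outcome. A weak association with the matrix could mean no effect, a noisy biomarker or a poor index. A stronger one could reflect rurality, which the article lists as a potential confounder and which is plausibly tied to nearby crop area.

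The index cannot serve as a standard or as a replicate. It estimates kilograms applied near the home from average rates and does not capture diet, an exposure route for which the article has built its own food frequency questionnaire.

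What is at stake is interpretation. A null result on gestational age, the primary outcome, could be presented as having passed a misclassification check when the check described does not test for misclassification.

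**Working it through.** **1. The plan's own figure.** Inputs from Statistical analysis: 1,800 analysable dyads, 5 covariates with combined R² 0.20, 80% power, type I error 0.05. With a 1-df F test, f² = R²/(1 − 0.20 − R²), noncentrality N·f² and denominator df N − 7, the detectable R² is 0.00348. This rounds to the stated 0.003. The noncentrality is 1,800 × 0.00348/0.79652 = 7.86.

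For the secondary outcomes, ln OR per SD ≈ (z for two-sided 0.0083 + z for 80% power)/√(N·p·(1 − p)). For congenital anomalies p = 54/1,800 = 0.03, so ln OR = (2.64 + 0.84)/√52.4 = 0.48 and OR = 1.62. For hypertensive disorders (288/1,800 = 0.16) OR = 1.25. The article states 1.3 to 1.7.

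**2. Can the outcome model detect misclassification?** Two settings were simulated (n = 2,000,000), with all variables standardised.

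- *Setting B, error present:* biomarker W has reliability 0.30, GIS index G has correlation 0.5 with true exposure, and the outcome has true slope 0.10.
- *Setting A, no error in the biomarker:* W equals true exposure, and G has its own association with the outcome, as confounding would produce.

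By hand for B: corr(W,G) = √0.30 × 0.5 = 0.274; cov(W,Y) = √0.30 × 0.10 = 0.0548; cov(G,Y) = 0.5 × 0.10 = 0.050. The joint coefficients are (0.0548 − 0.274 × 0.050)/(1 − 0.274²) = 0.044 for W and (0.050 − 0.274 × 0.0548)/(1 − 0.274²) = 0.038 for G. Setting A was built to have this same joint distribution.

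| | W, G coefficients (simulated) | Correlation of two urines |
|---|---|---|
| B: reliability 0.30 | 0.045, 0.037 | 0.30 |
| A: no error | 0.044, 0.038 | 1.00 |

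The outcome model cannot separate the two settings. A second urine does.

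**3. How much could be at stake?** The article gives no reliability, so a single-urine ICC of 0.2, 0.4 or 0.6 is **assumed**, with classical error. For the mean of k urines, λ = k·ICC/(1 + (k − 1)·ICC). Observed R² ≈ λ × true R². Because the article's odds ratios are per SD of the exposure variable, observed ln OR ≈ √λ × true ln OR. Power is for a true R² of 0.00348 at N = 1,800.

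| ICC | Urines | λ | Power | True R² needed for 80% | OR 1.62 appears as |
|---|---|---|---|---|---|
| 0.2 | 1 | 0.20 | 24% | 0.0174 | 1.24 |
| 0.4 | 1 | 0.40 | 43% | 0.0087 | 1.36 |
| 0.6 | 1 | 0.60 | 58% | 0.0058 | 1.45 |
| 0.2 | 3 | 0.43 | 45% | 0.0081 | 1.37 |
| 0.4 | 3 | 0.67 | 63% | 0.0052 | 1.48 |
| 0.6 | 3 | 0.82 | 72% | 0.0042 | 1.55 |

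Example: ICC 0.2 and three urines give λ = 0.6/1.4 = 0.43, and 1.62^√0.43 = 1.37.

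**The case against.** **A matrix could carry some information.** The reference that defines it is not at hand. If biomarker and GIS levels are cross-classified into concordant and discordant groups, or if the index is used as an instrument, indirect evidence is possible. In setting B the instrument ratio is 0.0493/0.2748 = 0.18 against a naive slope of 0.055, which recovers a reliability of about 0.3. This stands, but only if the index acts on the outcome solely through true exposure. The article does not state that assumption, and rurality threatens it. The conclusion is therefore limited to the method as worded.

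**A condensed article leaves detail to the analysis plan.** A reader might infer that the study has no check on attenuation and so cannot tell a true null from a diluted effect. The documents do not support this. A reliability analysis may sit in a plan that is not shown, the regression approaches are offered as examples, the article leaves room for methods suited to the data, and a direct GIS-biomarker comparison is already planned. The absence of an ICC is not the finding. The finding is a stated method that does not answer its stated aim.

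**Attenuation can be overstated.** A reader might shrink the log odds ratio by λ itself, so that 1.62 appears as 1.10 to 1.34 with one urine. That applies to a fixed exposure unit. The article works per SD, where √λ applies.

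**Repeat urines are not a clean answer.** This also stands. Enrolment runs to 20+6 weeks, early deliveries may precede the third collection, and a missed third-trimester urine may be taken after delivery. The number and timing of urines thus depend partly on gestational age at birth. Samples a trimester apart also mix true change with error, and fixed effects for trimester and season remove only average change.

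**Conclusion.** The aim and the method of the misclassification sentence do not match, and the sentence should be corrected. This follows from the text and from step 2 and needs no assumed reliability. The planned primary estimate is unaffected, because the matrix is an adjunct analysis; what changes is what may be claimed from it.

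The power and odds-ratio figures only illustrate why a valid check is worth having. They rest on the assumed ICC range, on classical non-differential error and on N = 1,800. They do not show that single-urine analysis is the plan for whole-pregnancy exposure.

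**What to change.** - **Reword.** Drop the claim that the outcome model of the matrix evaluates misclassification. Keep the matrix as an adjunct exposure analysis.
- **Evaluate misclassification from the urines.** For each herbicide, fit a mixed model to the repeated log concentrations with trimester and season as fixed effects and a random intercept per woman. Report ICC = between-woman variance/(between-woman + within-woman variance), beside the GIS-biomarker comparison already planned under Exposure assessment.
- **Sensitivity analysis for gestational age.** Give a regression-calibrated estimate for pregnancy-average exposure next to the uncorrected one. Let the calibration depend on each woman's number of urines, and add a check restricted to samples taken in a gestational window that all women in the analysis reach, because the number of samples depends on the outcome.

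The cost is a change of wording and a small analysis of data already planned, with no new collection. The downsides are wider intervals, reliance on a classical-error assumption, and no clean correction for trimester-specific exposure. For these reasons the calibrated estimate should not replace the main one.

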## Challenges and anticipated responses

While the Heartland Study is anticipated to be a relatively large cohort of at least 2000 pregnancy dyads, it may still be underpowered to identify associations between herbicides and some rare outcomes, such as stillbirth and specific congenital anomalies. Aggregation of related outcomes may be used to improve power where appropriate. For example, it may be appropriate to evaluate fetal death as an aggregate variable including stillbirth and miscarriage, which occur on a spectrum. Related congenital anomalies may be aggregated to achieve statistical power if appropriate.

This study is poised to make an important contribution to the existing knowledge about herbicide concentration. There may be limitations in the ability to detect important seasonal variations in concentration and sensitive windows for exposure, although recurrent urine samples are being collected throughout pregnancy and aggregate batches by phases of the growing season will be evaluated. The study will utilize the latest advancements in analytic techniques for urine biomarker analysis, providing an objective assessment of concentration. Multi-exposure modeling will be used to examine the combined effects of herbicide exposure. Geographic estimates of exposure will be used to augment biomarker data and allow for a more multidimensional exposure assessment. Through combined application of the techniques, the Heartland Study will fill important gaps in knowledge about herbicide exposures in the Midwest.

## Data Availability

At the end of the study, we plan to deposit data into a public data repository for use by other researchers as needed. Until data are deposited, we will entertain request for data sharing and collaboration.

## Abbreviations

BMI: Body Mass Index
EDD: Estimated Due Date
EGA: Estimated Gestational Age
EPA: United States Environmental Protection Agency
FFQ: Food Frequency Questionnaire
HELLP: Hemolysis, Elevated Liver Enzymes, Low Platelet Count
LMP: Last Menstrual Period
PSS: Perceived Stress Scale
PROM: Premature Rupture of Membranes
US: Ultrasound
USDA: United States Department of Agriculture
USGS: United States Geological Service
